**Outcome 2C):** Mean increase in maximum resting pressure by at least 50%.

**Objective 3) LUT, bowel and sexual functions (long-term TCSCS):** To test whether targeted long-term TCSCS (6-week trial) is safe and can improve urinary and faecal continence in humans with chronic SCI.

**Objective 3A)** To test whether targeted long-term TCSCS can improve urinary and faecal continence.

**Hypothesis 3A)** Long-term TCSCS will improve urinary and faecal continence. These improvements will be greater in individuals who complete intensive long term TCSCS compared to individuals who complete moderate long term TCSCS.

**Outcome 3A):** Mean decrease in the frequency of urinary and faecal incontinence by at least 50%.

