### Inclusion and Exclusion Criteria

#### *Inclusion:*

A participant with SCI must meet all of the following criteria in order to be eligible for inclusion:

1. Resident of British Columbia, Canada with active provincial medical services plan
2. Male or female, 18-65 years of age
3. Chronic traumatic SCI (non-progressive, with complete motor paralysis) at or above the T6 spinal segment.
4. >1-year post injury, at least 6 months from any spinal surgery.
5. Documented presence of bladder dysfunction
6. Documented presence of bowel or sexual dysfunction.
7. American Spinal Injury Association Impairment Scale (AIS) A, B.
8. Greater than or equal to antigravity strength in deltoids and biceps bilaterally
9. Hand function sufficient to perform Clean Intermittent Catheterization (CIC) or a committed caregiver to provide CIC for management of urinary bladder drainage.
10. Participants must have documented three days of bladder and bowel history prior to their baseline visit.
11. Willing and able to comply with all clinic visits and study-related procedures.
12. Able to understand and complete study-related questionnaires (must be able to understand and speak English or have access to an appropriate interpreter as judged by the investigator).
13. No painful musculoskeletal dysfunction, unhealed fracture, pressure sore, or active infection that may interfere with testing activities.
14. Medication dosage must be stable for period of 4 weeks prior to participation
15. Baclofen dose cannot exceed 60mg per day
16. Stable management of spinal cord related clinical issues (i.e., spasticity management).
17. Women of childbearing potential must not be intending to become pregnant, currently pregnant, or lactating. The following conditions apply:
  - a) Women of childbearing potential must have a confirmed negative pregnancy test prior to the baseline visit.
  - b) Women of childbearing potential must agree to use adequate contraception during the period of the trial. Effective contraception includes abstinence.

18. Must provide informed consent.

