#### *Bowel assessment*

- Neurogenic bowel dysfunction score (NBD Score)
- The modified Wexner fecal incontinence score (WIS)
- Time Needed for Bowel Movement (TNFBM), completed at home

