### *Low Urinary tract assessments*

- Neurogenic Bladder Symptom Score (NBSS): comprises 23 questions covering 3 domains, including incontinence (primary outcome, AIM 3A), storage & voiding, and specific consequences, as well as one question on QoL.
- The Incontinence-QoL (I-QoL): comprises 10 questions covering 3 domains, including avoidance and limiting behaviour, psychosocial impacts, and social embarrassment, which will be summarised as a total score. All scores, for each domain and a total, will be transformed into a continuous scale value.

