### *Bowel assessments*

- Neurogenic bowel dysfunction score (NBD Score) The NBD score is a measure of both constipation and fecal incontinence and was developed for and validated in the SCI population. This questionnaire comprises 10 questions focusing on defecation (i.e., frequency, duration, and clinical symptoms), constipation (i.e., use of aiding medication and digital stimulation), fecal incontinence (i.e., frequency, aiding medication, and flatus; and peri-anal skin problems. The consequential NBD score relates to four different neurogenic bowel dysfunction severity levels
- The modified Wexner fecal incontinence score (WIS): The WIS scale includes items that take into account type, frequency and extent to which fecal incontinence alters an individual's life, use of anti-diarrhea medications and the ability to defer defecation for 15 min.
- Time Needed for Bowel Movement: Participants will be asked to record the time from 'suppository insertion' to 'when bowel evacuation is completed', during their regular bowel movement at home.

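### Outcome 3A sets a 50% fall in incontinence frequency, but its named measure is a symptom score, no urinary episode count is scheduled after baseline, and no stated analysis addresses 50%

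*Protocol*

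**What the plan says.** Under Objectives, Hypotheses and Outcomes, the protocol gives Outcome 3A as "Mean decrease in the frequency of urinary and faecal incontinence by at least 50" per cent. Outcome 3C asks whether the 3A improvements persist 6 and 12 weeks after stimulation ends. Outcome 2C, for anorectal manometry, has a threshold of the same kind: "Mean increase in maximum resting pressure by at least 50" per cent.

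The Low Urinary tract assessments under Validated questionnaires describe the NBSS domains as "including incontinence (primary outcome, AIM 3A), storage & voiding, and specific consequences". The Bowel assessments describe two composites. The NBD score covers, among other things, "fecal incontinence (i.e., frequency, aiding medication, and flatus". Of the other composite the protocol says: "The WIS scale includes items that take into account type, frequency and extent to which fecal incontinence alters an individual's life".

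Inclusion criterion 10 reads: "Participants must have documented three days of bladder and bowel history prior to their baseline visit". The text for the treatment weeks, week 13, week 19 and week 25 does not mention this record again.

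The Statistical Plan analyses NBSS, NBD, I-QoL and IIEF-15 or FSFI by a two-way repeated-measures ANOVA comparing changes between the moderate and intensive groups. Urodynamics and an item called faecal continence severity are tested within groups by Wilcoxon signed-rank tests, from baseline to the end of treatment. Significance is P below 0.05.

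**The concern.** An outcome needs a quantity, a measurement of that quantity and an analysis that speaks to it. For 3A these do not line up. The outcome section names how often incontinence occurs; the questionnaire section names a domain score. The protocol gives no link by which a given percentage fall in that score means the same percentage fall in leakage. The stated tests can be significant at changes well short of one half.

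Two misreadings of the results become possible. A P-value below 0.05 could be reported as Outcome 3A having been met, or a 50% fall in a score could be presented as a 50% fall in episodes. Because 3C is defined by maintenance of the 3A improvements, it carries the same ambiguity into follow-up.

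**Working it through.** **The protocol's own figure.** The only computed sample size is 26, for voiding efficiency with short-term stimulation. The effect size is (58.2 − 37.8) / √((40.6² + 39.4²)/2) = 20.4/40.0 = 0.510. With power 0.80 and α = 0.05, a one-sided paired t-test gives 26 (power 0.812); a two-sided test gives 33. The figure reproduces, but it does not concern 3A. The Statistical Plan says there are no long-term data on which to base a power calculation.

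**What is collected after baseline.**
- Treatment weeks: time needed for bowel movement once a week (a duration), and ambulatory blood pressure.
- Week 13: urodynamics, neurological examination, NBSS, I-QoL, NBD, WIS, time needed for bowel movement, and the sexual and autonomic questionnaires.
- Weeks 19 and 25: the same questionnaires and bowel-movement time.

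Urinary leakage is not counted at any of these times. For the urinary half of 3A, the protocol describes only the NBSS domain score and I-QoL. For the faecal half, frequency is an item within NBD and WIS, and no item-level analysis is stated.

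**What the tests address.** The ANOVA is stated as a contrast of change between dose groups, so its stated comparison is of equal change. The signed-rank test has a null of no change. Neither has 50% in its hypothesis.

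**How far apart the two questions are.** Suppose percentage reduction in frequency were measured. Assumptions, none given in the protocol: 20 per group (the split of the 40 is not stated), every participant with some incontinence at baseline, SD of individual percentage reduction of 30, 50 or 80 points, two-sided 0.05, and a t-test standing in for the signed-rank test.

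SE = SD/√20 = 6.7, 11.2, 17.9. The smallest observed mean reduction significant against zero is t(0.975, 19) × SE, with t = 2.093. For the lower 95% limit to reach 50%, the observed mean must be 50 + t × SE.

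| SD (points) | Significant against 0 from | Lower limit at 50% from | P(significant), true reduction 30% | P(observed mean ≥ 50%), true reduction 30% |
|---|---|---|---|---|
| 30 | 14.0% | 64.0% | 0.99 | 0.001 |
| 50 | 23.4% | 73.4% | 0.72 | 0.04 |
| 80 | 37.4% | 87.4% | 0.36 | 0.13 |

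The last column is 1 − Φ((50 − 30)/SE). With all 40 pooled, significance against zero needs only 9.6%, 16.0% or 25.6%.

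**The case against.** The strongest reply is that this is a pilot and proof-of-concept study. The protocol lists 3A as an outcome without attaching a decision rule, and a 50% figure can be reported descriptively in an analysis plan that is not shown here. The between-group ANOVA also matches the second part of Hypothesis 3A, that intensive stimulation does better than moderate. All of that stands, and it limits the severity. It does not remove the point: the two sections name different quantities for the same aim, and an analysis plan cannot supply urinary counts that were not collected.

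A reader might also infer more than the text supports.
- That only composite scores are collected after baseline. Urodynamics, bowel-movement time and ambulatory blood pressure are collected too, and a coarse faecal frequency might be taken from NBD or WIS items.
- That every test is against zero change. This fits the signed-rank tests; the ANOVA's stated contrast is between groups.
- That WIS is the faecal measure for 3A. Nothing says so, and the Statistical Plan does not name it.
- That percentage change is undefined because incontinence is not an entry criterion. This holds for an individual with none at baseline; a percentage fall in the group mean remains defined.
- That the three-day history already counts leaks. The criterion does not say what it records.

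The Schedule of Events cited in the Overview is not shown, so the absence of a repeat record rests on the visit-by-visit text.

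**Conclusion.** The point holds in limited form. The protocol is inconsistent about what Outcome 3A is, its visit text schedules no urinary episode count after baseline, and no stated analysis refers to frequency, percentage change or 50%. A significant result under the stated tests would not show that 3A is met. The gap could be wide: with the assumed SDs and 20 per group, a mean reduction of 14% to 37% would pass a test against zero. Those figures illustrate the difference between the two questions and do not predict this trial's results.

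The faecal half is less affected than the urinary half, because some frequency information is collected. Outcome 2C shares the mismatch between its 50% and a test of no difference. No size is given for it, because the protocol supplies no variability for resting pressure. The correction should be made, but the defect does not undermine the study as a pilot.

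**What to change.** Either of two changes would resolve 3A.

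1. Restate Outcome 3A as mean change, with 95% CI and by dose group, in the NBSS incontinence domain and in one named faecal incontinence score. Remove the references to frequency and to 50%. This costs wording only.
2. Keep 3A as written. Repeat the three-day bladder and bowel record, with leakage episodes explicitly counted, at weeks 13, 19 and 25, and specify the same counting for the record before baseline. Report the percentage change in group mean episode frequency with its 95% CI set against 50%. The cost is three more short home diaries per participant.

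Outcome 3C should then refer to whichever quantity is chosen. For Outcome 2C, report the percentage change in maximum resting pressure between stimulation on and off, with its 95% CI set against 50%, and state that P below 0.05 is not evidence of an increase of at least 50%. An interval that merely excludes no change would not be enough for that claim.

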**Objective 3B) To test whether targeted long-term TCSCS can improve sexual function.**

**Hypothesis 3B:** Long-term TCSCS will improve sexual function in male and female participants, with an emphasis on overall sex life satisfaction. These improvements will be greater in individuals who complete intensive long term TCSCS compared to individuals who complete moderate long term TCSCS.

**Outcome 3B:** Mean improvement in satisfaction with participant's overall sexual life.

**Objective 3C) To assess persisting effects of long-term TCSCS on LUT, bowel and sexual function.**

**Hypothesis 3C):** The longevity of the beneficial effects on LUT, bowel and sexual function, after cessation of TCSCS, will be greater in the group that received intense stimulation versus the group that received moderate stimulation.

**Outcome 3C):** Maintained improvements in urinary and faecal incontinence (AIM 3A) and sexual function (AIM 3B) at 6 and 12 weeks after the cessation of TCSCS.

### Research design

This is a proof of concept study to demonstrate the clinical efficacy of real-time (short-term) TCSCS (proof-of-concept) to improve LUT, and bowel in adults with chronic SCI. This is also a pilot trial phase and a proof-of-concept study to test clinical long term efficacy of TCSCS to improve LUT, bowel and sexual function in adults with chronic SCI.

### Statistical Plan

Statistical analysis on LUT, bowel and sexual function will be performed (n = 40 with SCI).

A sample size calculation was performed using G\*power, version 3.0.10, with power set at 0.8 and  $\alpha$  at 0.05. Data from participants that match our inclusion criteria (n = 5, level of lesion C5 – T10, motor-complete AIS, A or B) were used from a recent TCSCS study. A minimum sample of 26 participants is required to detect a significant change in voiding efficiency [voided volume / (voided volume + post-void residual volume)] with short-term TCSCS (stim-off =  $37.8 \pm 40.6\%$  vs. stim-on =  $58.2 \pm 39.4\%$ , effect size = 0.510). Presently, there are no long-term TCSCS data with LUT and bowel outcomes, consistent with those proposed in this protocol, to facilitate a meaningful power calculation. Therefore, given this is a pilot trial study, and in order to account for drop out with long-term TCSCS, we aim to investigate 40 individuals with SCI (n = 40, C5 – T6). Short-term TCSCS effects on UDS parameters (AIM 2A) as well as ARM testing (AIM 2C) with or without different stimulation configurations will be assessed using a repeated measures non-parametric analysis of variance (ANOVA), i.e. Kruskal–Wallis test. Data from the repeatability portion of the study (AIM 2A) will be assessed within (same session) and between (different sessions) visits (2 and 3) using a repeated measures non-parametric ANOVA. TNFBM will also be assessed using a repeated measures non-parametric ANOVA.

Long-term TCSCS: Differences in continuous variables for questionnaire data (NBSS, NBD Score, I-QoL, IIEF-15 or FSFI) in AIM 3 will be assessed using a two-way repeated measures [baseline, immediately post long term TCSCS as well as post-interventional follow up at 6 and 12 weeks] ANOVA comparing changes between moderate and intensive TCSCS. Furthermore, UDS testing as well as 'faecal continence severity' (baseline and end of TCSCS 6-week period) will be assessed using Wilcoxon signed-rank tests within

groups. A P-value less than 0.05 will be considered statistically significant. A complete thematic analysis will be performed to collect contextual qualitative data from the sexual health interview.

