## Objectives, Hypotheses and Outcomes

**Objective 1:** To establish specific spatiotemporal activation maps for TCSCS at various spinal cord segments known to be involved in LUT and bowel control.

**Hypothesis 1:** In light of recent findings on the efficacy of spinal cord stimulation to improve bowel and LUT function, the optimal setting for motor responses (i.e. mapping) will be revealed during TCSCS.

**Primary outcome 1:** An individualized TCSCS map (i.e. location and stimulation parameters) to elicit optimal skeletal muscle activation corresponding to spinal cord segments involved in LUT and bowel control

**Objective 2:** To test whether targeted short-term TCSCS is safe with respect to cardiovascular consequences (e.g. autonomic dysreflexia) and can repeatedly improve LUT and bowel functions in humans with chronic SCI.

**Objective 2A) LUT function (safety/efficacy):** To test whether targeted short-term TCSCS is safe and can induce detrusor contractions (*voiding function*) while relaxing the EUS, i.e. to avoid DSD and independently enhance EUS tone (*storage function*).

**Hypothesis 2A):** In light of recent findings demonstrating TCSCS improves LUT function, we hypothesize that short-term TCSCS will improve voiding and storage functions without ACVEs.

**Outcome 2A):** Changes from baseline in the following UDS parameters for bladder capacity/compliance:

- i. Volume at the first sensation
- ii. Intravesical pressure (Pves) at the first sensation
- iii. Volume at the leakage point
- iv. Pressure at the leakage point
- v. Maximum bladder volume
- vi. Pves at the maximum bladder volume

**Objective 2B) LUT function (repeatability of TCSCS to improve UDS parameters):** To test whether targeted short-term TCSCS will repeatedly improve UDS parameters across different stimulation sessions.

**Hypothesis 2B):** TCSCS will elicit reproducible improvements in UDS parameters without ACVEs.

**Outcome 2B):** Reproducibility of changes within urodynamic parameters during stimulation will be assessed during two consecutive urodynamic procedures. UDS parameters for bladder capacity/compliance:

- i. Volume at the first sensation
- ii. Pves at the first sensation

**Objective 2C) Bowel function (safety/efficacy):** To test whether targeted short-term TCSCS is safe and can result in an immediate increase in anorectal pressure.

**Hypothesis 2C):** TCSCS will increase anorectal pressure without adverse cardiovascular effects.

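### The only power calculation is for voiding efficiency, which is not a listed outcome, and its minimum of 26 reproduces only as a one-sided paired t-test; the two-sided equivalent is 33

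*Protocol*

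**What the plan says.** The Statistical Plan reports a G*Power calculation with "power set at 0.8" and alpha at 0.05. It concludes: "A minimum sample of 26 participants is required to detect a significant change in voiding efficiency". The inputs are voiding efficiency of 37.8 (SD 40.6)% with stimulation off and 58.2 (SD 39.4)% with it on, summarised as "effect size = 0.510". Neither the test nor its sidedness is named.

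On the source of these figures the plan says: "Data from participants that match our inclusion criteria (n = 5, level of lesion C5 – T10, motor-complete AIS, A or B) were used". Inclusion criterion 3 reads: "Chronic traumatic SCI (non-progressive, with complete motor paralysis) at or above the T6 spinal segment".

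The same section assigns short-term urodynamic and anorectal effects to a repeated-measures non-parametric ANOVA, labelled Kruskal–Wallis, across stimulation configurations. It gives Wilcoxon signed-rank tests to the before-and-after urodynamic comparison in the long-term phase. The decision rule is "A P-value less than 0.05 will be considered statistically significant".

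Outcome 2A is defined as "Changes from baseline in the following UDS parameters for bladder capacity/compliance", followed by six items: volume and pressure at first sensation, at leakage and at maximum bladder volume. Outcome 2B repeats the first two. The target enrolment is 40.

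**The concern.** A power statement tells the reader which comparison the trial is sized to answer. Here the comparison is one that the trial does not list. Objective 2A does mention voiding, but its outcomes describe storage volumes and pressures, so nothing that the trial is set to report carries the stated 80% power.

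The number itself also looks small. An effect of about half a standard deviation in a paired design usually needs more than 26 people with a two-sided test at 0.05. If 26 rests on an undeclared one-sided test, the stated minimum is too low for a plan that elsewhere speaks only of a significant change at P < 0.05. Two inputs deserve the same scrutiny: the effect size uses the spread between people rather than the spread of within-person differences, and the five source participants are said to match eligibility criteria that their lesion range does not fit.

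**Working it through.** **Inputs** (all from the Statistical Plan): means 37.8 and 58.2; SDs 40.6 and 39.4; effect size 0.510; power 0.8; alpha 0.05; stated minimum 26. The within-person correlation r is not given.

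**Effect size.** Mean difference = 58.2 − 37.8 = 20.4. Pooled SD = √((40.6² + 39.4²)/2) = 40.0. Then 20.4/40.0 = 0.510, as stated.

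**Reproducing 26.** For a paired t-test, power comes from the noncentral t distribution with n − 1 degrees of freedom and noncentrality 0.510·√n. At n = 26 the noncentrality is 0.510 × 5.099 = 2.60.

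| n | One-sided power | Two-sided power |
|---|---|---|
| 25 | 0.797 | 0.687 |
| 26 | 0.812 | 0.705 |
| 32 | 0.880 | 0.798 |
| 33 | 0.889 | 0.811 |
| 40 | 0.936 | 0.882 |

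The smallest one-sided n with power of at least 0.80 is 26, an exact match. The smallest two-sided n is 33. None of the other forms tried gives 26: an independent-groups comparison needs 48 per group one-sided or 61 two-sided (normal approximation), and a two-condition repeated-measures F test with r = 0.5 needs 33. A two-sided signed-rank test needs about 34, but only as an approximation that assumes normal data.

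**What 0.510 assumes as a paired effect.** The SD of the differences is √(40.6² + 39.4² − 2·r·40.6·39.4), and the paired effect is 20.4 divided by it. The r values below are assumptions.

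| r | SD of differences | Paired effect | Two-sided n for 80% |
|---|---|---|---|
| 0.3 | 47.3 | 0.431 | 45 |
| 0.5 | 40.0 | 0.510 | 33 |
| 0.7 | 31.0 | 0.658 | 21 |

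Only r of about 0.5 makes 0.510 a paired effect. At r = 0.6 the two-sided n would be 27, but the effect would then be 0.57 rather than the stated 0.510.

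**Endpoint against outcomes.** Voiding efficiency is voided volume divided by voided plus residual volume. Outcomes 2A and 2B contain neither volume. Outcome 2C is anorectal resting pressure, 3A is frequency of incontinence, 3B is sexual satisfaction, and 3C is maintenance of 3A and 3B. The Urodynamics section describes filling, a prefill to 50–75% of capacity, stimulation, and stopping at fullness, leakage, the blood-pressure limit or the patient's request. It describes no voiding phase and no measurement of the residual.

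**Source data against eligibility.** A lesion range of C5–T10 includes at least one participant at T10, which is below T6. The Statistical Plan itself gives C5–T6 for the 40 to be studied.

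**The case against.** Four objections have weight.

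First, 26 is not a miscalculation: it follows exactly from the stated inputs if the test is one-sided, and Hypothesis 2A is directional. That stands. The fault is an unstated test and sidedness that do not fit the rest of the section. A directional hypothesis does not by itself declare a one-sided test, and the calculation is worded "to detect a significant change in voiding efficiency".

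Second, 70% and 33 belong to a two-sided paired t-test, which the protocol does not plan. A reader might take 70% as the power of the planned short-term analysis. The documents do not support that. The planned test is a non-parametric ANOVA over an unstated number of configurations, on a percentage with mean 38 and SD 41 that is hardly normal. For illustration, a parametric repeated-measures F test with f = 0.255 and r = 0.5 has power 0.705 at 26 with two conditions and 0.796 with three. The figures 70% and 33 are the two-sided counterpart of the protocol's own calculation and no more.

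Third, a correlation of 0.5 may have been entered deliberately, since it also returns 0.510. That is possible; the gap is that it is not reported.

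Fourth, this is a declared pilot, and 40 enrolled still gives about 88% two-sided power under the same inputs. This stands and limits the consequence. A reader might go further and infer that the drop-out margin is overstated, because 40 lies closer to 33 than to 26. That does not follow: the protocol ties drop-out to long-term stimulation, gives no rate, and places the short-term tests at Visits 4–6, before that phase begins.

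**Conclusion.** The point holds at moderate severity. The endpoint mismatch is the more consequential part: the protocol's one power statement attaches to a measure that is neither a listed outcome nor measured in the procedure as described, so no listed outcome is powered. The minimum of 26 is the one-sided paired t-test answer (power 0.81). The one-sided reading is inferred from the exact match, because the protocol states no sidedness. The two-sided paired t-test has about 70% power at 26 and needs 33, given effect 0.510 and an assumed correlation of about 0.5. The requirement moves between 45 and 21 as the assumed correlation goes from 0.3 to 0.7. The claim that the five source participants match the inclusion criteria contradicts criterion 3.

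A reader might infer that the trial is too small. The documents do not show that: enrolment is 40, long-term power is expressly not claimed, and two-sided power at 40 is about 88% on the protocol's own effect size. That 88% concerns voiding efficiency only and shares the assumed correlation.

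**What to change.** In the Statistical Plan:

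1. Name the test, the sidedness and the assumed within-person correlation behind the calculation.
2. Restate the minimum as 33 (two-sided paired t-test, alpha 0.05, effect 0.510, r = 0.5), with about 70% power at 26 and about 88% at 40. If the signed-rank figure of 34 is quoted, mark it as an approximation under normality.
3. Either state that the calculation is for voiding efficiency and that the listed urodynamic outcomes are unpowered, or base the calculation on one of the listed outcomes.
4. Correct the statement that the source participants match the inclusion criteria, given C5–T10 against T6 or above.

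These are text changes, and enrolment of 40 is unaffected. The cost is a less favourable minimum and an open statement that the listed outcomes are unpowered. Basing the calculation on a listed outcome would also need variability data for it, which the protocol does not give. Adding voiding efficiency as an outcome is a different matter: the Urodynamics section has no voiding phase or residual measurement, so it would mean changing the procedure and reconciling it with the stopping text there.

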### Urodynamics

Participants will undergo standard clinical procedures for UDS, including cystometry with water at 21°C and a filling rate of < 30 mL per minute through a 6F double lumen catheter with the participants in the supine position. Abdominal pressure will be measured with a 10F intrarectal balloon catheter. Pelvic floor electromyography will be recorded during cystometry with a surface electrode placed on the

perineum. Filling will be stopped when the participants report a sensation of fullness, at the moment of urine leakage, if blood pressure reaches levels of 180/110 mmHg, or per the request of the patient.

Following the standard clinical assessment UDS we will perform UDS with TCSCS. To assess the efficacy of short-term TCSCS' on LUT function, we will first prefill the bladder (i.e. 50-75% of cystometric capacity from the first UDS) without eliciting detrusor overactivity or autonomic dysreflexia. Then, TCSCS (as described above) will be delivered for 60 s each interspersed with 30 s rest (i.e. no stim) to optimize the configuration for each individual. Stimulation frequency and location will be guided by the results of the Baseline EMG Mapping of Spinal Cord Segments performed during visit 3.

TCSCS will be stopped when the participants report a sensation of fullness, at the moment of urine leakage, if blood pressure reaches levels of 180/110 mmHg, or per the request of the patient.

Urodynamics will be performed by a trained clinician (MD or RN) under the supervision of [name] (MD), who is a urologist.

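### The short-term urodynamic and anorectal analysis is an omnibus test across stimulation conditions, but the hypotheses and the sample size concern a directional on-versus-off contrast

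*Protocol*

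**What the plan says.** The Statistical Plan assigns the short-term effects on urodynamic parameters (AIM 2A) and on manometry (AIM 2C) to a single type of analysis: effects "with or without different stimulation configurations will be assessed using a repeated measures non-parametric analysis of variance (ANOVA"). It names no comparison of stimulation on against off, no direction, and no rule for which configuration counts.

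The hypotheses under Objectives, Hypotheses and Outcomes are directional. For 2A, "we hypothesize that short-term TCSCS will improve voiding and storage functions without ACVEs". Objective 2C asks whether stimulation "can result in an immediate increase in anorectal pressure", and Outcome 2C is an increase of at least 50% in maximum resting pressure.

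The sample size rests on two conditions, stim-off and stim-on: "A minimum sample of 26 participants is required to detect a significant change in voiding efficiency", with "effect size = 0.510".

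The configuration is individual. The Urodynamics section delivers stimulation in 60-second trains, "interspersed with 30 s rest (i.e. no stim) to optimize the configuration for each individual", with location and frequency guided by the participant's Visit 3 map. The ARM section is similar.

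**The concern.** An omnibus rank test has the null that all conditions have the same distribution. It is rejected when a configuration improves function, when one worsens it, and when configurations differ among themselves with none better than off. Its p-value therefore does not answer the question that 2A and 2C put.

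The second difficulty is power. The test compares condition labels that must mean the same thing in every participant. If the labels are electrode sites and the best site differs between people, which is the premise of an individual map, each label carries only a fraction of the benefit. A null result would then say little about whether the individually chosen configuration works. The study is described under Research design as a proof of concept for short-term efficacy, so this is the question it most needs to answer.

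**Working it through.** **Inputs.** Power: "with power set at 0.8 and" alpha at 0.05 (Statistical Plan; "A P-value less than 0.05 will be considered statistically significant"). Voiding efficiency 37.8 ± 40.6% off and 58.2 ± 39.4% on, effect size 0.510, minimum n 26, planned n 40 (Statistical Plan). Four cathode positions (TCSCS section). The number and coding of configurations in the urodynamic and manometry comparison are not stated, so four sites and two are both tried as assumptions.

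**1. The Protocol's own figure.**
- Difference: 58.2 − 37.8 = 20.4 points. SD of the paired difference: 20.4 / 0.510 = 40.0.
- Implied within-person correlation: (40.6² + 39.4² − 40.0²) / (2 × 40.6 × 39.4) = 1600.72 / 3199.28 = 0.50.
- Paired t-test, noncentral t, effect 0.51: one-sided 0.05 gives n = 26 (power 81.2%), an exact match. Two-sided gives n = 33, with 70.5% power at n = 26.

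So the sizing is a two-condition paired contrast. The omnibus test is a different analysis.

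**2. Simulation set-up.** Normal data, SD 1 per condition, within-person correlation 0.5. The SD of a paired difference is then √(2 × (1 − 0.5)) = 1, so a shift of 0.51 is the Protocol's effect size. Five conditions (off plus four sites), two-sided 0.05, 3,000 runs. The omnibus test is taken as Friedman, the rank test suited to repeated measures; naming Kruskal–Wallis for such data is a separate error.

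**3. Does rejection show benefit?** Friedman rejection at n = 40:

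| Truth | Rejects |
|---|---|
| No condition differs | 5–6% |
| One site better by 0.51 | 83% |
| One site worse by 0.51, none better | 84% |
| All four sites worse by 0.51 | 82% |

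The p-value alone cannot separate the last three rows.

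**4. Power when the responsive site varies.** Each participant gains 0.51 at one site, with sites spread evenly. The average gain per label is 0.51 / 4 = 0.1275 with four sites and 0.51 / 2 = 0.255 with two.

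| n = 40 | Friedman by site | Own configuration vs off, always the right one |
|---|---|---|
| Four sites | 8% | 88% |
| Two sites | 25% | 88% |

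With four sites and correlations of 0.3 to 0.75, Friedman gives 7.5% to 11.5% and the contrast 75% to 99%. At correlation 0.5, a gain of 1.0 gives Friedman 17.5% and a gain of 1.5 gives 29%.

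**5. If the chosen configuration is not always the right one.** With a 75% hit rate the mean gain is 0.75 × 0.51 = 0.3825, and signed-rank power at n = 40 is about 60%. With 50% it is 0.255 and about 32%. With 25%, which is chance among four sites, it is about 11%.

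**6. Where the omnibus test loses little.** If everyone responds at every site, power is 83% against 88%, a loss of 5 points. If the conditions are off, own voiding configuration and own storage configuration, it is about 80% against 88%, a loss of 8 points.

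**The case against.** Four points on the other side have force.

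- A reader might infer from the 84% rejection under harm that the test has a false-positive problem. It does not. One condition truly differs, so rejecting is correct, and under the true null the rate is 5–6%. A two-sided signed-rank test would also reject in about 85% of trials if its configuration were worse by 0.51. What remains is narrower: a two-condition contrast shows its direction with the result, and an omnibus p-value does not.
- A reader might also infer that the planned test is bound to miss an individualised benefit. The Protocol does not define the condition levels, and the TCSCS section ties the four sites to mapping (AIM 1). Coding by own configuration is a natural reading and removes most of the loss. The 8% is the worst case for the omnibus test, and the 88% is the best case for the contrast because it assumes perfect selection. No passage supports perfect selection from a skeletal-muscle map.
- It is tempting to add that voiding and storage configurations push the urodynamic parameters in opposite directions. Objective 2A seeks both effects, but no passage says that the listed parameters will move that way.
- Follow-up contrasts and estimates are commonly left to an analysis plan, which is not shown and may contain them. That explains missing detail. It does not cure the mismatch between the analysis that the Protocol names and its own hypotheses and sizing.

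**Conclusion.** The concern holds in a limited form. The analysis named for 2A and 2C does not test the directional on-versus-off claims, and it is not the comparison on which the study was sized. That part rests on the text alone and needs no simulation.

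The power loss is conditional. For an effect of 0.51 at n = 40 it runs from about 5 to 8 points (shared response, or coding by own configuration) to a fall to about 25% or 8% (coding by site, responsive site spread evenly over two or four sites). The achievable alternative is up to about 88%, about 60% at a 75% hit rate and 32% at 50%. These figures assume normal data, a correlation of 0.5 and all 40 participants contributing. The point merits a change to the plan, but it does not show that the short-term stage must fail.

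**What to change.** Make the primary short-term analysis a within-participant contrast of the participant's own configuration against stim-off, by Wilcoxon signed-rank test with a Hodges–Lehmann estimate and 95% confidence interval, separately for urodynamics and manometry. State for each parameter which direction is improvement. Where both a voiding and a storage configuration are used, test each against off on its own parameters.

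The configuration tested must be identified on data other than those that test it, since picking the best run and testing it on the same data overstates benefit. The planned visits allow this: the configuration selected in UDS 1 can be tested in UDS 2, and the Visit 3 map can identify the one for manometry. This decides only which recorded runs enter the primary test and leaves the clinical choice of stimulation settings as it is.

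Keep the omnibus comparison as exploratory and define its condition levels. The change is to analysis wording, with no added visits or participants. The costs are that differences between configurations become exploratory and that the confirmatory urodynamic test uses one session.
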